**Questionnaire for Subject:**

The subject's own perception of the smell will be documented and graded in VAS of 1-10 and compared to his normal perception of his smell and of the environment perceptive as he sees it.

The subject will also be questioned about his compliance to the required hygiene procedure of his study arm.

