**Study Design and Title:**

Assessing Odor Level when Using PrePex for HIV Prevention: A Prospective, Randomized, Open Label, Blinded Assessor Trial to Improve Uptake of Male Circumcision.

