**Independent Blinded Reviewers (herein: Smellers):**

3 smellers will be chosen to participate in the study to perform a smell test using smell detector device; the "Nasal ranger" device, see the following link for technical information:

[http://www.nasalranger.com/Operations/Nasal%20Ranger%20Operations%20Manual%20v6.2.pdf](http://www.nasalranger.com/Operations/Nasal Ranger Operations Manual v6.2.pdf)

The Smellers will go through a short training in order to know how to operate the device and to assess their skills.

On day 0 pre procedure, the smellers will use the Nasal Ranger device to smell each of the 100 subject's genitals (baseline). Below are the room and procedure requirements. Only after the smelling procedure, will the subject undergo PrePex procedure.

The subjects will arrive to the clinic on days 3, 5 and 7 in order to document their odor levels.

On the Removal day (Day 7), the smellers will attend the Removal procedures and use the Nasal Ranger device. Below are the room and procedure requirements:

- 2 rooms will be used during the study which will have the same constant conditions (same room with no initial smell, same window, same distance from the penis: 30 cm)
- Usage of Nasal ranger device by trained personnel only
- The subjects will be randomized for their turn to enter the room
- When the smeller enters the room, the subject face will be covered and he will not wear his clothes but hospital garment
- After all 100 subjects were smelled by all 3 smellers, the subjects will be randomized again for their turn to enter the room (new randomization)
- When the smeller enters the room, the subject face will be covered and he will not wear his clothes but hospital garment
- The room should be aired between subjects
- The smelling will be always in the same distance from the genitals, by measuring with a ruler, 30 cm distance between the genitals and the end of the "Nasal Ranger"
- Each Smeller will be asked separately to grade the smell as he performs it as it is shown in the "Nasal ranger"
- Only at the end of the smelling procedure will the foreskin and device be removed.

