**Secondary Objectives**

- To determine an absolute odor level per each arm
- To determine a penis cleaning procedure guidelines safety and efficacy
- To determine the subject's perception of odor per study arm
- To compare the different perception of the subject’s partner relating to the odor when examine 3 arms of patients undergoing PrePex circumcision with same personal hygiene and with different foreskin hygiene techniques.

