***Statistical Analysis:***

All data will be presented via descriptive statistics. Binary data such as adverse events success/fail criteria will be presented as a count and percentage together with an exact 95% confidence interval. Adverse event rates will be compared descriptively with the reported rates of similar treatments. Continuous data will be represented by a mean, standard deviation, median, minimum and maximum together with 95% confidence intervals for the means.

Study Flow

Screen 120 candidates

100 enrolled subjects

Randomization

Arm 1 -33 subjects

- Standard PrePex
- General hygiene instructions
- Foreskin hygiene general instructions – daily shower

Arm 2 -33 subjects

- Standard PrePex
- General hygiene instructions
- Foreskin specific hygiene instructions – daily soapy water with syringe
- **Follow up visits days 3, 5 & 7**
- Subject questionnaires
- Odor tests by 3 Blinded smellers
- Partner questionnaire – on days 3, 5 & 7
- Removal on day 7
- A random sample of subjects were evaluated a second time on day 7
- Safety - AEs

Arm 3 – 33 subjects

- Standard PrePex
- General hygiene instructions
- Foreskin specific hygiene instructions - daily chlorhexidine with syringe

|  | **Randomization & Screening Visit** | **Applying Visit** |  |  | **Removal Visit** |
| --- | --- | --- | --- | --- | --- |
| **Visit #** | **1** | **2** | **3** | **4** | **5** |
| **Day (D)/week (w)** | **–7 to D0** | **D0** | **D3** | **D5** | **D7** |
| Informed consent | X |  |  |  |  |
| Randomization | X |  |  |  |  |
| Inclusion/exclusion criteria | X |  |  |  |  |
| Medical history & Demography | X |  |  |  |  |
| Current medication including pain killers | X | X |  |  | X |
| Genital examination and potential pictures | X | X | X | X | X |
| Device apply |  | X |  |  |  |
| Foreskin Removal |  |  |  |  | X |
| Device Removal |  |  |  |  | X |
| Subject's subjective pain, tingling and discomfort evaluation |  | X | X | X | X |
| Expected Side effects and AE |  | X | X | X | X |
| Smellers test |  | X | X | X | X |
| Questionnaires for patients & for sub group female partners (between days 5-6) |  |  | X | X | X |
| Statistical analysis of data |  |  |  |  |  |

Table of Contents

[Study Synopsis 2](#__RefHeading___Toc344626056)

[Schedule of Events 8](#__RefHeading___Toc344626057)

[1. Clinical background 12](#__RefHeading___Toc344626058)

[2. STUDY OBJECTIVES AND PURPOSE 15](#__RefHeading___Toc344626059)

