
**Follow-Up:**

The subjects will arrive for follow up visits on days 3, 5 & 7 in order to document the odor level.

There will be an interview phone call with the subject's partner (where possible) to assess hers perception of the smell. It will be conducted during days 5-6.

No follow up is required post Removal visit.

1. **Independent Blinded Reviewers (herein: Smellers):**

3 smellers will be chosen to participate in the study to perform a smell test using smell detector device; the "Nasal ranger" device, see the following link for technical information:

[http://www.nasalranger.com/Operations/Nasal%20Ranger%20Operations%20Manual%20v6.2.pdf](http://www.nasalranger.com/Operations/Nasal Ranger Operations Manual v6.2.pdf)

The Smellers will go through a short training in order to know how to operate the device and to assess their skills.

1. **Questionnaire for Subject:**

The subject's own perception of the smell will be documented and graded in VAS of 1-10 and compared to his normal perception of his smell and of the environment perceptive as he sees it.

The subject will also be questioned about his compliance to the required hygiene procedure of his study arm.

1. **Questionnaire for partners:**

The perception of the subject's spouse/partner will be documented where possible, via a phone interview.

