## 8.3 Statistical analysis

**Sample size:**

The intention is to obtain at least 100 evaluable subjects under Rwanda ethical responsibility (RNEC), determining to use the most deducted calculation setting and to maintain allocation ratio of 1:1:1 between the 3 study arms (33 per arm).

A sample size for the study was determined based on the two-sample t-test. In order to detect an effect size of 0.7 (Cohen's D) with 80% and at and a 5% level of significance between any two groups a sample size of 33 subjects is required. In the study each subject will have a smell test repeated by three different smellers this will be in order to examine the variability in odor sensation between different clinicians. Given this design and the three groups that will be compared, a statistically more powerful model (repeated measures ANOVA) is used instead of a t-test, and thus the study will be appropriately powered.

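### The subject's odor VAS is to be compared with his normal smell, but the questionnaire starts on Day 3, so as scheduled that reference can only be a retrospective, unblinded judgement

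*Protocol*

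**What the plan says.** The synopsis, under Questionnaire for Subject, has the man's perception of his smell "graded in VAS of 1-10 and compared to his normal perception of his smell", with a second comparator concerning how he thinks his surroundings perceive it. Section 6.3 repeats the instruction: "The subject's own perception of the smell will be documented and graded in VAS of 1-10". Neither place says when or how the normal reference is obtained.

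In the schedule of events in the synopsis, the row "Questionnaires for patients & for sub group female partners (between days 5-6" is blank at Visit 1 (Day -7 to Day 0) and at Visit 2 (Day 0), and marked at Days 3, 5 and 7. The Study Flow lists the subject questionnaires under "Follow up visits days 3, 5 & 7". Device application is marked at Visit 2 only, and randomization at Visit 1.

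The smellers are treated differently. Under Independent Blinded Reviewers: "On day 0 pre procedure, the smellers will use the Nasal Ranger device to smell each of the 100 subject's genitals (baseline", with placement only afterwards.

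The title describes "A Prospective, Randomized, Open Label, Blinded Assessor Trial", so the blinding it claims is that of the assessors. The second list of secondary objectives in the synopsis includes "To determine the subject's perception of odor per study arm". Section 8.3.3 plans to correlate odor levels with the subject and partner questionnaires.

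**The concern.** A comparison with a man's normal smell needs some record or judgement of that normal. From Day 0 to Day 7 he wears a device that makes the foreskin necrotic, so his usual state cannot be observed at any visit where the questionnaire is given. He must reconstruct it. The smell he notices at the time can colour that reconstruction, and so can his belief in the washing method he was given, possibly to a different degree in each arm.

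At stake is the interpretability of any statement about how far subjects found their odor changed from usual. A rating not taken before placement cannot be recovered later by an analysis plan, so this belongs in the protocol's schedule.

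**Working it through.** **Timing, set side by side**

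| Item | Visit 1 (D-7 to D0) | Visit 2 (D0) | D3 | D5 | D7 |
|---|---|---|---|---|---|
| Randomization | X | | | | |
| Device application | | X | | | |
| Smellers' test | | X (before placement) | X | X | X |
| Pain, tingling and discomfort | | X | X | X | X |
| Subject questionnaire (odor VAS) | | | X | X | X |

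The only subject-reported row marked on Day 0 concerns pain, tingling and discomfort, not odor. The first odor rating by the subject follows three days of wear. That the reference is retrospective is an inference, since the protocol does not describe how it is elicited, but the schedule leaves no other route.

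**The plan's own figure**

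The point does not rest on the sample size, but the number per arm is used below. The basis in section 8.3 is "In order to detect an effect size of 0.7 (Cohen's D) with 80% and at and a 5% level of significance between any two groups", giving 33 per group.

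- Normal approximation: n = 2 × (1.960 + 0.842)² / 0.7² = 32.04, rounded up to 33. This reproduces the stated figure.
- t-test calculation: n = 33.02, with power 79.97% at 33 per group. This agrees for practical purposes.

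**Precision forgone without a baseline**

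Inputs: 33 per arm (sections 8.2 and 8.3); two-sided 95% confidence (section 8.3.1); r, the correlation between a pre-placement VAS and a follow-up VAS, which the document does not give and which is assumed to lie between 0.3 and 0.7.

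- Without a baseline: half-width = t(64) × √(2/33) = 1.998 × 0.2462 = 0.492 SD.
- With the baseline as covariate: multiply by √(1 − r²), ignoring the one degree of freedom spent.

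| Assumed r | √(1 − r²) | Residual variance removed | Half-width (SD) |
|---|---|---|---|
| none | 1 | 0% | 0.492 |
| 0.3 | 0.954 | 9% | 0.469 |
| 0.5 | 0.866 | 25% | 0.426 |
| 0.7 | 0.714 | 49% | 0.351 |

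These figures measure the precision that a baseline could buy. They do not measure bias in a retrospective reference, for which the document gives no input.

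**The case against.** The strongest reply is that the sentence can be read as a single anchored question at each visit: how do you smell now, against your usual smell and against how others perceive it? That form needs no earlier score. The protocol defines no change score, the cited objective asks only for perception by arm, and the questionnaire itself is not shown. Section 2 does not list subject perception among its objectives, and section 3 speaks only of odor levels as a guide to patients' acceptability. All of this stands, and it is why the protocol cannot be said to contradict itself: it never promises a pre-placement subject rating. But an anchored question still asks the man to remember his usual smell during wear, so the weakness in the reference remains.

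A reader might go further and infer that the arm comparison on the subject's VAS is invalid without a baseline. It is not. Allocation is randomized, and raw scores at Days 3, 5 and 7 can be compared directly. A baseline adds precision and an observed reference; it is not a condition for validity. Nor does the point reach the primary odor measure, because the smellers have their own Day 0 reading.

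Two objections to the remedy also stand. Randomization is at Visit 1, so a man rating himself on Day 0 may already know his arm. And a single rating records that day's smell, which depends on recent washing and is not quite the same as his usual smell.

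Finally, the precision gain is small at r = 0.3, and would be smaller still if most men rate themselves near the bottom of the scale before placement.

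**Conclusion.** The point holds as a limited weakness in design. As scheduled, the comparison with normal smell in the subject's self-report rests on a retrospective judgement made during device wear by a man who is not blinded. It concerns one secondary measure. The primary odor readings, the sample size and the randomized comparison of raw VAS scores are not affected.

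The direction and size of any bias in the reference cannot be determined from the document, and nothing in it shows that such bias would differ between arms; that remains a possibility. The precision forgone runs from slight (0.49 to 0.47 SD) to material (0.49 to 0.35 SD) across the assumed correlations of 0.3 to 0.7. The change is worth making because it is cheap and because the missing rating cannot be obtained once the device is on.

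**What to change.** Add the own-odor VAS item to the schedule of events before device placement. The better place is Visit 1, after consent and before the allocation envelope is opened, so that the rating is free of knowledge of the arm. Failing that, take it on Day 0 before placement, alongside the smellers' baseline.

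In the synopsis and section 6.3, under Questionnaire for Subject, name this score as the reference for normal smell. Compare arms on the Day 3, 5 and 7 VAS adjusted for it. If no pre-placement rating is added, state plainly that the reference is retrospective.

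The cost is one questionnaire item at a visit the man already attends and one more mark in the schedule, with no extra visit or staff. The change does not remove unblinded reporting at Days 3, 5 and 7, and the single rating should be described as that day's smell.

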**Questionnaire for partners:**

The perception of the subject's spouse/partner will be documented where possible, via a phone interview.

**PrePex Procedure:**

The subjects will go through a standard PrePex procedure which is described below.

The PrePex Operators and Assistants must be formally trained in the Rwanda PrePex Center of Excellence or by qualified PrePex trainers from Rwanda with the most up to date training program and certified as PrePex Operators and Assistants.

After assessment of eligibility and after the subject has signed the informed consent form, the subject will be enrolled in the study.

A **standard PrePex procedure** is described below:

The procedure will be carried out in a clean non-sterile environment. The subject will undergo sizing of the penis sulcus with the PrePex Sizing Plate. The penis will be cleaned by red Povidone-Iodine solution or other disinfection solution (Chlorahexidine, etc.) with the foreskin stretched backwards to expose the inner skin for the disinfection solution. Then the foreskin will be dried with a dry gauze. The Operator will then mark the circumcision line with a clean skin marker and then the Assistant will open the corresponding sized package of the PrePex device, and will load the Elastic Ring on to the Placement Ring. Then, Lidocaine 5% dermal cream will be applied on the inner foreskin. The Placement Ring with the Elastic Ring will be placed on the penis shaft and the foreskin tip will be stretched open to the sides by the operator hands, the operator may select to use a dry gauze to affirm the grip. Then, the Inner Ring will be applied through the stretched foreskin and over the glans penis (hereinafter, "glans") so that it will be placed fixed over the sulcus behind the glans (the base of the glans). At this point, the foreskin around the inner ring is held tight by the Assistant, and the Placement Ring and Elastic-Ring are approximated to the Inner Ring by the Operator. The foreskin is then adjusted to fit the circumcision marking line to the Elastic-Ring. Then, the Elastic-Ring is released from the Placement Ring on to the Inner Ring groove, initiating homeostasis. The procedure is then completed. Medication based on 400mg Ibuprofen is given to the subject to use at home if needed. The subject will then take part in a formal discharge session in a class room, where he will be instructed to return for a follow up visit and in any non sustained situation and to take painkillers in case of pain. The device will remain in situ for 7 days, at which the subject will return for a removal visit (i.e. if placed on Monday, removed on the following Monday). In case subjects arrive on day 5 or 6 and require removal of the device and foreskin, it is for the medical decision of the center managing physician to perform the removal if he/she thinks the removal is safe at this day. Those subjects will be followed for the procedure safety and efficacy. The foreskin is removed using sterile scissors, the Elastic Ring is removed using a #10 scalpel (surgical blade), and then the Inner Ring is extracted using a spatula or fingers, depending on the thickness of the foreskin. The area might be compressed with gauze for 30 seconds to avoid oozing and clear exudates. Following the removal process, the circumcision area will be dressed with a non-adherent sterile pad for 2 days, the subject will receive one dressing pad for home to change in case the dressing gets wet. The subject will then take part in a formal discharge session in a class room, where he will be instructed to turn to his local health center in any non sustained situation. Following the 2 days (day 9) the subject will remove the dressing on his own at home. The subject will be instructed to return in any non sustained situation, regardless of the follow-up visit.

**Follow-Up:**

The subjects will arrive for follow up visits on days 3, 5 & 7 in order to document the odor level.

There will be an interview phone call with the subject's partner (where possible) to assess hers perception of the smell. It will be conducted during days 5-6.

No follow up is required post Removal visit.

**Primary Objectives:**

- Safety - To determine the adverse events rate per foreskin cleaning technique per study arm
- Efficacy - To compare the different odor levels when examine 3 arms of patients undergoing PrePex circumcision with same personal hygiene and with different foreskin hygiene techniques

**Secondary Objectives**

- To determine an absolute odor level per each arm
- To determine a penis cleaning procedure guidelines safety and efficacy
- To determine the subject's perception of odor per study arm
- To compare the different perception of the subject’s partner relating to the odor when examine 3 arms of patients undergoing PrePex circumcision with same personal hygiene and with different foreskin hygiene techniques.

**Statistical Considerations:**

**Sample size:**

The intention is to obtain at least 100 evaluable subjects under Rwanda ethical responsibility (RNEC), determining to use the most deducted calculation setting and to maintain allocation ratio of 1:1:1 between the 3 study arms (33 per arm).

A sample size for the study was determined based on the two-sample t-test. In order to detect an effect size of 0.7 (Cohen's D) with 80% and at and a 5% level of significance between any two groups a sample size of 33 subjects is required. In the study each subject will have a smell test repeated by three different smellers this will be in order to examine the variability in odor sensation between different clinicians. Given this design and the three groups that will be compared, a statistically more powerful model (repeated measures ANOVA) is used instead of a t-test, and thus the study will be appropriately powered.

***Statistical Analysis:***

All data will be presented via descriptive statistics. Binary data such as adverse events success/fail criteria will be presented as a count and percentage together with an exact 95% confidence interval. Adverse event rates will be compared descriptively with the reported rates of similar treatments. Continuous data will be represented by a mean, standard deviation, median, minimum and maximum together with 95% confidence intervals for the means.

Study Flow

Screen 120 candidates

100 enrolled subjects

Randomization

Arm 1 -33 subjects

- Standard PrePex
- General hygiene instructions
- Foreskin hygiene general instructions – daily shower

Arm 2 -33 subjects

- Standard PrePex
- General hygiene instructions
- Foreskin specific hygiene instructions – daily soapy water with syringe
- **Follow up visits days 3, 5 & 7**
- Subject questionnaires
- Odor tests by 3 Blinded smellers
- Partner questionnaire – on days 3, 5 & 7
- Removal on day 7
- A random sample of subjects were evaluated a second time on day 7
- Safety - AEs

Arm 3 – 33 subjects

- Standard PrePex
- General hygiene instructions
- Foreskin specific hygiene instructions - daily chlorhexidine with syringe

|  | **Randomization & Screening Visit** | **Applying Visit** |  |  | **Removal Visit** |
| --- | --- | --- | --- | --- | --- |
| **Visit #** | **1** | **2** | **3** | **4** | **5** |
| **Day (D)/week (w)** | **–7 to D0** | **D0** | **D3** | **D5** | **D7** |
| Informed consent | X |  |  |  |  |
| Randomization | X |  |  |  |  |
| Inclusion/exclusion criteria | X |  |  |  |  |
| Medical history & Demography | X |  |  |  |  |
| Current medication including pain killers | X | X |  |  | X |
| Genital examination and potential pictures | X | X | X | X | X |
| Device apply |  | X |  |  |  |
| Foreskin Removal |  |  |  |  | X |
| Device Removal |  |  |  |  | X |
| Subject's subjective pain, tingling and discomfort evaluation |  | X | X | X | X |
| Expected Side effects and AE |  | X | X | X | X |
| Smellers test |  | X | X | X | X |
| Questionnaires for patients & for sub group female partners (between days 5-6) |  |  | X | X | X |
| Statistical analysis of data |  |  |  |  |  |

Table of Contents

[Study Synopsis 2](#__RefHeading___Toc344626056)

[Schedule of Events 8](#__RefHeading___Toc344626057)

[1. Clinical background 12](#__RefHeading___Toc344626058)

[2. STUDY OBJECTIVES AND PURPOSE 15](#__RefHeading___Toc344626059)

